### Recruitment

Students will be recruited in two waves, in October 2015 (beginning of Michaelmas term) and January 2016 (beginning of Lent term). Figure 1 shows the participant timeline.

**Figure 1 BMJOPEN2016012300F1:**
[figure not shown]
Participant timeline.

The evaluation will be advertised widely in the student community at the University of Cambridge. Posters will be put up in the University buildings. Facebook and Twitter study accounts will be used. Colleges will circulate an email presenting the study and inviting students to attend the information sessions at the beginning of both terms. The students' Mindfulness Society has agreed to direct students who approach them with an interest in learning mindfulness to the information sessions. All materials will display a dedicated email address for contacting the study team.

Advertising will focus on letting students know about the study and directing them to a dedicated website or to information sessions that will take place in the first weeks of each term. Both the website and the information sessions will provide prospective participants with detailed information about the study and consent procedures.

### Blinding and randomisation procedures

After agreeing to take part, students will be emailed with a link to the online baseline questionnaire. Only those who complete the baseline questionnaire will be randomised. Simple randomisation will be carried out remotely by the survey software (Qualtrics) using computer-generated random numbers. Participants will be informed of their allocation automatically after completing the baseline questionnaire. This way the allocation process will be concealed from researchers.

Participants randomised to the intervention group will be requested to state which of the seven mindfulness session times on offer they would be able to attend. Then, to minimise attrition, an allocation optimisation programme will be run with these data to assign as many students as possible to one of their preferred course times.

Participants cannot be blind to allocation because of the nature of the intervention. However, outcome assessment will be blind because data collection is carried out remotely and automatically. The primary analysis will be carried out by a statistician blind to which arm is the intervention, and other variables/information which could be used to identify intervention arm data. Mindfulness courses will include participants who are not part of the trial (consisting of up to 60 interested students distributed evenly across courses so that 4–5 students out of 30 per course are not part of the study), and the mindfulness teacher will not be told who is and who is not a participant in the study.

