**Methods and analysis:**

At least 550 University of Cambridge students free from active crises or severe mental illness will be randomised to joining an 8-week mindfulness course or to mental health provision as usual (one-to-one allocation rate). Psychological distress will be measured using the Clinical Outcomes in Routine Evaluation Outcome Measure at baseline, postintervention, examination term and 1-year follow-up. Other outcomes are use of mental health services, inability to sit examinations or special circumstance requests, examination grades, well-being, altruism and coping measured with ecological momentary assessment. Outcome assessment and intention-to-treat primary analysis using linear mixed models adjusted for baseline scores will be blind to intervention allocation. We will also conduct per-protocol, subgroup and secondary outcome analyses. An Independent Data Monitoring and Ethics Committee will be set up. We will systematically monitor for, and react to, possible adverse events. An advisory reference group will comprise student representatives, members of the University Counselling Service and other student welfare staff.

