### Trial design

The study will be a pragmatic randomised controlled evaluation with two parallel arms and a one-to-one allocation rate testing the superiority of mindfulness training provision to no provision. University of Cambridge students will be randomised to joining a mindfulness course during the term they are starting plus mental health provision as usual (PAU), or to PAU alone. PAU comprises access to individual counsellors, mental health advisors and psychiatrists at the University of Cambridge Counselling Service (UCS), as well as access to welfare staff in the University colleges (this provision varies across colleges, but can include college nurse, counsellor, welfare officer or tutor) and National Health Services (NHS). Those allocated to PAU alone will be offered a mindfulness course 1 year later, providing they are still students at the University.

The mindfulness intervention was offered for two terms before study initiation; this allowed the intervention to become established before evaluating it, and provided feasibility and acceptability data. The present proposal is partly based on the experience during those two terms. Interest in the courses doubled teaching capacity. An opportunistic randomised evaluation was therefore considered reasonable.

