### Outcomes and data collection

Several outcomes will be measured and compared between mindfulness and control groups to assess the effects of the course. The primary outcome will be a self-reported global measure of psychological distress assessed during the examination term, the most stressful period of Cambridge students' academic year. Secondary outcomes are exploratory assessments that may help to describe mindfulness' effects in more focused ways. Outcomes are listed in table 1.

**Table 1 BMJOPEN2016012300TB1:** MSS study outcomes

Outcome	Source/measure	Variable type	Collection points
Use of mental health services	Self-reported	Nominal	One-year follow-up
Use of University Counselling Service	Routinely collected	Nominal	Baseline, 1-year follow-up
Perceived impact of problems on academic performance	Self-reported	Ordinal	Examination term
Examination grades and rankings	Routinely collected	Ordinal	Examination term
Special circumstances requests for examinations	Routinely collected	Nominal	Examination term
Inability to sit examinations (intermissions and degrading)	Routinely collected	Nominal	Examination term
Psychological distress	Self-reported: CORE-OM	Treated as interval	Baseline, postintervention, examination term, 1-year follow-up
Well-being	Self-reported: WEMWBS	Treated as interval	Baseline, postintervention, examination term, 1-year follow-up
Altruism	Behavioural	Ordinal	Postintervention, examination term, 1-year follow-up
Coping	Self-reported	Ordinal	Baseline (Lent), examination term
Physical activity	Behavioural (sensor)	Ratio	Baseline (Lent), examination term
Sleep times	Behavioural (sensor)	Ratio	Baseline (Lent), examination term

CORE-OM, Clinical Outcomes in Routine Evaluation Outcome Measure; MSS, Mindful Student Study; WEMWBS, Warwick-Edinburgh Mental Well-being Scale.

Psychological distress will be measured using the Clinical Outcomes in Routine Evaluation Outcome Measure (CORE-OM), a 34-item generic questionnaire which was designed to assess efficacy and effectiveness across multiple disciplines offering psychological therapies, and has been widely used with UK university students. It is scored on a five-point scale ranging from 0 (not at all) to 4 (most or all the time). The total score range is 0–136; this is usually divided by number of completed items to form a total mean score. CORE-OM has good convergent validity, internal and test–retest reliability and sensitivity to change.^14^

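### Outcome assessment is called blind because collection is automated, but the primary outcome and the other self-reported outcomes are rated by participants who know their allocation

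*Protocol article*

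**What the plan says.** Under Blinding and randomisation procedures, the protocol article says that "Participants will be informed of their allocation automatically after completing the baseline questionnaire". Later in the section it accepts that "Participants cannot be blind to allocation because of the nature of the intervention", and the next sentence reads: "However, outcome assessment will be blind because data collection is carried out remotely and automatically". The section then adds that "The primary analysis will be carried out by a statistician blind to which arm is the intervention".

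The abstract (Methods and analysis) joins the two claims: "Outcome assessment and intention-to-treat primary analysis using linear mixed models adjusted for baseline scores will be blind to intervention allocation". It does not mention that participants know their arm.

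Under Outcomes and data collection, "The primary outcome will be a self-reported global measure of psychological distress assessed during the examination term", and Table 1 gives the source of psychological distress as "Self-reported: CORE-OM". The comparator is provision as usual with a delayed offer: "Those allocated to PAU alone will be offered a mindfulness course 1 year later, providing they are still students at the University".

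**The concern.** On a self-completed questionnaire the participant is the assessor. Whether assessment is blind then depends on what the participant knows, not on how the answers reach the database. The reason given, remote and automatic collection, shows that no interviewer or researcher can steer the ratings. It does not show that the ratings are made without knowledge of allocation, and the protocol itself says they are not.

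The abstract and methods therefore credit the primary comparison with a protection against detection bias that the design cannot give. The target difference is small (0.3 SD), the comparator does nothing to mask allocation, and the result is meant to inform the University's provision and policy elsewhere. A reader who takes the statement at face value, especially from the abstract alone, would put more trust in a modest CORE-OM difference than the design supports.

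**Working it through.** No figure in the protocol decides this point, so the main check sets its statements side by side.

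1. **Who rates the primary outcome?** The participant (Outcomes and data collection; Table 1).
2. **Does that person know the arm?** Yes. Allocation is disclosed after the baseline questionnaire, which is before every post-baseline measurement. The comparator, usual provision with a course a year later, cannot disguise it.
3. **What does remote, automatic collection change?** It takes the researcher out of the collection step. The answers to 1 and 2 stay the same.
4. **Which outcomes are affected?** In Table 1, CORE-OM, WEMWBS, use of mental health services, perceived impact on academic performance, and coping are self-reported. Use of the University Counselling Service, examination grades and rankings, special circumstances requests and inability to sit examinations are routinely collected. Physical activity and sleep times come from sensors. Altruism is behavioural, but it is a keep-or-donate choice made by a participant who knows the arm.
5. **Is the other half of the claim sound?** Yes. Data management describes an anonymised copy for an independent statistician who is kept from information that would identify the arms. Nothing contradicts this.

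**Illustration of what is at stake.** The bias sizes below are assumptions; the documents give none.

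- Analysed per arm: 275 × (1 − 0.20) = 220 (Sample size).
- Standard error of the difference in SD units, without baseline adjustment: √(2/220) = 0.0953.
- With no true effect and a bias of b SD, the two-sided rejection rate at 0.05 is 1 − Φ(1.960 − b/0.0953) + Φ(−1.960 − b/0.0953).
- Conversion to CORE-OM points uses the SD of 0.59 from Sample size.

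| Assumed bias b (SD) | CORE-OM points (b × 0.59) | Shift b/0.0953 | Chance of p<0.05 |
|---|---|---|---|
| 0 | 0 | 0 | 5% |
| 0.05 | 0.03 | 0.52 | 8.2% |
| 0.10 | 0.06 | 1.05 | 18.2% |
| 0.20 | 0.12 | 2.10 | 55.5% |

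Biases of 0.10 and 0.20 SD are one-third and two-thirds of the 0.3 SD target.

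**The case against.** The strongest reply is that nothing is hidden. The sentence just before the claim says participants cannot be blind, and blinding is impossible with this intervention. That is correct, and it limits the point to a wrong label and a wrong reason. It does not rescue the statement, because the abstract carries the claim without the disclosure and the methods draw a conclusion that the disclosure contradicts. Nor can the point be put down to condensing a fuller document into an article: it is a positive statement that is wrong as written.

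A second reply is that the calculation does not measure the error. This also stands. Any bias would come from unblinded self-report and would be the same after rewording. The figures ignore the planned baseline adjustment. In a pragmatic comparison of provision with no provision, which disclaims determining specific effects, an expectation that truly lowers distress is arguably part of the effect being estimated. Only differential reporting is measurement bias.

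A reader might also go further than the documents allow, in three ways:

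- *That the trial's blinding fails as a whole.* The analyst's blinding is described consistently and is untouched.
- *That only routinely collected outcomes escape self-report, and that these are blind.* Table 1 also lists sensor and behavioural measures. No section says that the Student Registry or the counselling service is unaware of allocation. Service use and special circumstances requests also depend on what unblinded students do.
- *That a CORE-OM effect should count only if routine records agree.* The protocol calls its secondary outcomes exploratory, sizes the trial on CORE-OM alone, and measures different constructs with grades and service use. Agreement would not validate a CORE-OM difference, and disagreement would not refute one.

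**Conclusion.** The point holds as an error of statement. The abstract and the blinding section attribute blind outcome assessment to a trial whose primary outcome, and four other self-reported outcomes in Table 1, are rated by participants who know their arm. This rests on the protocol's own text and needs no outside assumption. It does not touch the sample size, the primary analysis model or the statistician's blinding, and it is not a finding of concealment.

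The consequence cannot be sized from the documents. If differential reporting were 0.05 to 0.20 SD, the chance of a nominally significant CORE-OM difference with no true effect would be about 8% to 55% instead of 5%, assuming 220 analysed per arm and no gain from baseline adjustment. These figures show why the label matters for a 0.3 SD target. They are not an estimate of the bias in this trial. The correction should be made, but it is a matter of wording and interpretation.

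**What to change.** Replace the claim in both the abstract and Blinding and randomisation procedures with text such as: *The primary and other self-reported outcomes are rated by participants who know their allocation; remote automated collection prevents researcher influence on the ratings; the primary analysis is carried out by a statistician blind to arm.*

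Describe the routinely collected and sensor outcomes as *not self-reported*, and do not call them blind. Add to Strengths and limitations of this study that a CORE-OM difference is open to response (detection) bias because participants know their arm.

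The cost is a few sentences and a less favourable risk-of-bias statement. No change to design, data collection or analysis is needed.

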### Inducements for participation

There will be no inducements for completing the mindfulness courses. However, to promote participant retention and as a token of appreciation for completing all the study questionnaires, a total of £11 will be available to each student across the study in the form of Amazon vouchers as explained above. In addition, there will be a prize draw of 5×£100 Amazon vouchers among those who complete 50% or more smartphone questions plus all the questionnaires. Students who complete 50% or more smartphone notifications will be offered individual feedback on their coping, sleep and physical activity patterns after the study ends.

### Public engagement

Involving stakeholders in the choice of question and design of the research is important to ensure relevance.^23^ The study plans presented here were reviewed by a group comprising representatives from the UCS, the Academic Division, student representatives and college tutors. A focus group with students who completed mindfulness courses taught before the trial was consulted about the study plans before submission to the Ethics Committee for approval.

An advisory reference group will be put together comprising student representatives, members of the University Counselling Service and other student welfare staff. They will meet three times a year. Study researchers will attend these meetings and present updates. Reference group terms of reference will be available on request.

### Statistical methods

The primary analysis will consist of an intention-to-treat analysis comparing the primary outcome, CORE-OM during the examination period, between arms adjusted for baseline scores, routine demographics and timing of receipt of intervention relative to examinations (as some will have done the course during Michaelmas 2015 and others during Lent 2016). Multiple imputation will be used as long as there are <40% missing data in the corresponding variable to ensure validity of imputations and will be applied only to variables with expected missing completely at random and missing at random patterns (ie, when there are no reasons to think that the pattern may be missing not at random). This imputation will take account of other CORE-OM data points and routinely collected demographics. We will also conduct a per-protocol analysis (minimum dose assumed to be 50% attendance of sessions^24^) excluding individuals in the control group who have engaged in meditation elsewhere during the follow-up period preceding outcome measurement.

Outcomes measured at three time points (CORE-OM, WEMWBS and altruism, measured at postintervention, examination period and 1-year follow-up) will be analysed using a repeated measures design with a treatment by time interaction term to study their trajectories through the academic year and to determine whether differences (ie, intervention effects) were consistent over time. Repeated measures analyses will also be performed with ecological momentary assessment data to study outcome trajectories, pattern changes during the examination period and differences between arms.

CORE-OM and WEMWBS data will be combined to explore the broader spectrum of distress/well-being if taken as a continuum.^25^ Subscales of the CORE-OM (subjective well-being, problems symptoms, functioning, risk/harm) will also be explored as secondary outcomes, and results reported with and without correction for multiple testing. Multilevel models will be used to assess academic degrees and academic rankings as any student may sit more than one examination.

The following predefined subgroup analyses will be conducted on the primary outcome by using interaction tests:^26^
By degree, as most have examinations during the examination term but some do not;By year of study, to explore whether results differ for last year students, a different subpopulation as control group final year students will not be offered mindfulness a year later;By baseline CORE-OM: those initially worse may drive change;By gender: there is evidence of differential impact;^10^By amount of home practice during and after course in intervention group participants;By prior meditation experience (prior 8-week course or +50 hours spent meditating in the past—an 8-week course translates into 10–50 hours) as only novices may experience a change.

In order to assess how our sample compares against the student population in the UK, demographic and normative well-being/distress data will be obtained from the literature and compared with baseline values in our sample. A comparison of our baseline data with the profile of students attending the University Counselling Service will also be performed where possible to evaluate where our sample lies in the range between community and clinical student samples.

All statistical analyses will be conducted at an α level of p=0.05 (two-sided). Linear mixed models will be used for the analyses. Assumptions will be tested and diagnostic plots will be explored to assess model fit. Descriptive statistics for continuous variables will be summarised using mean/SD and median/IQR. Discrete variables will be summarised by proportions.

It is expected that the clustering effect will be negligible: although this is a group intervention, the work is highly personal, all the courses are taught by the same teacher, each course includes students from different colleges and courses, and the ‘session hopping’ option introduces variability. However, we will compute intraclass correlation by analysing session attendance patterns to see whether there is any clustering effect. If there is one, we will adjust for it using multilevel techniques.

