## Introduction

### Background and rationale

University students show elevated levels of stress. Although mental illness rates among first year students appear to be lower than those of the general population, they surpass general population rates when undergraduates get to their second year.^1^ Students report academic pressure as the biggest trigger of their mental health problems.^2^ University Counselling Services in the UK have noted the constant increase in the proportion of students seeking help in recent years.^3^
^4^ At the University of Cambridge, 8.5% of the students required access to counselling in 2014. An effective preventative intervention is needed to help students cope better with academic life and develop resilience.

Mindfulness interventions have been shown to reduce stress and prevent depression in clinical and non-clinical populations.^5^
^6^ Secular mindfulness training involves paying attention to the present moment on purpose and non-judgmentally.^7^ It is popular among students and increasingly used to support them in the UK.^8^ However, there is little evidence on the effectiveness of offering mindfulness training to this population or of any adverse effects. Previous randomised trials assessing mindfulness for supporting university students generally suffer from small sample sizes, lack of follow-up, low methodological quality and poor reporting.^9^ The largest good-quality study randomised 288 medical and psychology Norwegian students to mindfulness-based stress reduction or a waitlist and found moderate postintervention effects on psychological distress and subjective well-being.^10^ A recent systematic review which meta-analysed nine randomised and non-randomised studies found that mindfulness significantly reduced anxiety among university students (d=0.73; 95% CI 1.00 to 0.45).^11^ A good-quality and adequately powered randomised evaluation including the wider spectrum of university students is needed to confirm previous findings, extend the follow-up period and provide a more complete view of the potential impact (positive and negative) of the provision of mindfulness training on university student life. The University of Cambridge Vice-Chancellor's Endowment Fund is supporting such evaluation for use by services, funders and policymakers, as well as to inform the University's own decisions about the provision of mindfulness for students.

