Students' subjective well-being will be assessed using the Warwick-Edinburgh Mental Wellbeing Scale (WEMWBS), a questionnaire that captures a broad conception of well-being. It consists of 14 items, each scored on a five-point scale ranging from 1 (none of the time) to 5 (all of the time). The WEMWBS has good validity, internal consistency and test–retest reliability with a sample of UK students (n=354) and general population (n=2075).^15^

Mental health services use will be assessed by asking students whether during the examination term they have requested help with mental health issues and stress from a range of resources (eg, psychiatrist, Samaritans). Participants will also be asked to what extent such problems may have impacted on their academic performance (eg, To what extent do you have problems affecting your study?) and whether in their view their academic course workload was manageable. Data on inability to sit examinations will be provided by the Student Registry. The UCS will provide the research team with information about which participants used their services and how frequently they were used.

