Process measures will involve: (1) registering attendance at mindfulness courses (register taken) and asking why sessions were missed (routine practice for UCS); (2) asking students whether they did their mindfulness homework during the course and how much they have practised after the course, including whether they became members of the Mindfulness Society; (3) for students who abandon the study (ie, fail to complete questionnaires or contact us saying they wish to quit the study), information on why they have done so will be requested; (4) participants in the control group will be asked whether they have practised mindfulness elsewhere during the follow-up period.

Apart from the baseline measurements outlined in table 1, the following baseline data will be collected in order to compare the sample with the student population, and to run subgroup analyses: (1) students' prior experience with meditation and mindfulness; (2) demographic data provided by the student registry (eg, disability, ethnicity, socioeconomic classification). All baseline data will be collected before randomisation.

Questionnaires will be web-based. Privacy issues related to accessing student records and collecting data from smartphone sensors were explored in a focus group with students who completed mindfulness courses taught before the trial. Students felt these methods were acceptable.

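### The predictors named for imputing examination-term CORE-OM leave out University records of difficulty that the trial will hold on non-responders, so missing at random is a weaker assumption than it need be

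*Protocol article*

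**What the plan says.** The Statistical methods section of the protocol sets three conditions for imputation.

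- Amount missing: "Multiple imputation will be used as long as there are <40% missing data in the corresponding variable".
- Mechanism: imputation "will be applied only to variables with expected missing completely at random and missing at random patterns".
- Predictors: "This imputation will take account of other CORE-OM data points and routinely collected demographics".

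The Outcomes and data collection section describes further data that reach the trial without the student answering anything. Table 1 lists "Special circumstances requests for examinations" as routinely collected in the examination term, and lists intermission and degrading in the same way. The text adds: "Data on inability to sit examinations will be provided by the Student Registry". On counselling it says: "The UCS will provide the research team with information about which participants used their services and how frequently they were used". Table 1 places the counselling data at baseline and 1-year follow-up. WEMWBS is a questionnaire collected at the same four visits as CORE-OM.

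For students who abandon the study, "information on why they have done so will be requested". No use of these reasons in the imputation is stated.

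**The concern.** Whether data are missing at random depends on what the imputation conditions on. Here the missing variable is self-reported distress during examinations, and a student in difficulty at that time may well be less likely to complete a questionnaire. A request for special circumstances or an intermission plausibly predicts both a high score and a missing one, which is the usual reason for using a variable as an auxiliary predictor.

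Under the stated list, two students with the same completed CORE-OM scores, the same demographics and the same arm receive the same imputed distribution, even if one has intermitted and the other has not. Imputed scores for non-responders would then tend to be too low. If this error differs between arms, it passes into the primary treatment effect.

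The design makes a difference between arms possible. Participants know their allocation. Intervention students receive emails around each class and are contacted when they miss one, and the protocol describes no such contact for controls. It does not say which arm would lose more struggling students.

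**Working it through.** **Scale.** No figure in the plan depends on the predictor list, so the sample-size inputs serve only for scale: 0.3 SD, two-sided 5%, 90% power, 550 students (275 per arm), 20% loss and an SD of 0.59 points. The standard two-sample formula gives 234 evaluable students per arm for 90% power. The plan expects 275 × 0.8 = 220 completers per arm, which gives 88.2% power, close to the stated 90%.

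**Why the arms matter.** For each arm, error in the mean = share missing × (imputed mean − true mean of non-responders). Bias in the treatment effect = error in the intervention arm − error in the control arm. Equal errors cancel.

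**Simulation** (400,000 students per scenario, in SD units). These assumptions are not in the documents:

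- The treatment effect is −0.3 SD at postintervention and in the examination term.
- The correlation between CORE-OM time points is 0.5 or 0.7.
- A record of difficulty has a latent correlation of 0.5 with the examination-term score. Its prevalence is set at 8.5% or 20% of controls, which gives about 7.5% or 18% over both arms. The lower value follows the Background section ("8.5% of the students required access to counselling in 2014"); the higher is a guess.
- About 20% of scores are missing overall. Among students with a record, 50% are missing in both arms, or 65% in control and 35% in intervention. Among the others, (0.20 − 0.5 × 0.085)/(1 − 0.085) = 17.2%, or (0.20 − 0.5 × 0.20)/(1 − 0.20) = 12.5%, are missing.
- Imputation is by regression within arm, from baseline CORE-OM and, where held, the postintervention score. The effect is then estimated with adjustment for baseline.

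Bias without the record as a predictor (imputed estimate minus full-data estimate):

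| Students with a record | Correlation | Postintervention score held for non-responders | Equal dropout | 65% v 35% |
|---|---|---|---|---|
| 7.5% | 0.5 | none | 0.005 | 0.024 |
| 7.5% | 0.5 | all | 0.004 | 0.022 |
| 7.5% | 0.7 | none | 0.004 | 0.019 |
| 7.5% | 0.7 | all | 0.003 | 0.015 |
| 18% | 0.5 | none | 0.007 | 0.046 |
| 18% | 0.5 | all | 0.006 | 0.043 |
| 18% | 0.7 | none | 0.006 | 0.032 |
| 18% | 0.7 | all | 0.004 | 0.030 |

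Runs with half of the postintervention scores held fall within 0.003 of these rows. With the record in the imputation model, the bias is at most 0.002 throughout. That is partly by construction, because simulated dropout depends only on the record and the arm.

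**One scenario in full** (18%, correlation 0.5, no postintervention score, equal dropout). Responders average −0.212. Non-responders truly average 0.114, but are imputed at −0.129 without the record and 0.110 with it. CORE-OM alone closes (−0.129 + 0.212)/(0.114 + 0.212) = 0.083/0.326 = 25% of the gap. In the most favourable scenarios it closes about 60%. Averaged over both arms, the error in the mean is 0.193 × (−0.129 − 0.114) = −0.047 SD, but it nearly cancels between arms and leaves 0.007 SD in the treatment effect.

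**Relative size.** 0.003/0.3 = 1% and 0.007/0.3 = 2%; 0.015/0.3 = 5% and 0.046/0.3 = 15%. In CORE-OM points the largest bias is 0.046 × 0.59 = 0.027.

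**Other runs.** A separate simulation imputed from baseline only, with 19% of controls and 14% of intervention students carrying a record. It gave −0.294 against a true −0.30 with 45% missing among them in both arms. With 55% in control and 35% in intervention it gave −0.267, a bias of 0.033/0.30 = 11%. The table omits the 1-year score. In a similar set-up (correlation 0.6, 55% v 35%), adding the postintervention and 1-year scores cut the bias from about 0.026 to 0.020 SD. At n = 550, adding the record and its interaction with arm cost no precision (SD of the estimate 0.080 v 0.079).

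**The case against.** The strongest reply is that the sentence on predictors is not expressly exhaustive. It stands in a condensed article, and a fuller auxiliary list may be in an analysis plan that is not shown. That stands as far as it goes. But the article does choose which predictors to name, and among the routine data it names only demographics.

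Second, the plan does not impute whatever the mechanism. It withholds imputation where missing not at random is suspected, and it asks for reasons for leaving. That also stands. Yet a narrow predictor list makes the plan's own condition harder to meet, so the clause is a reason to widen the list.

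Third, the bias is modest. The standard error at 220 completers per arm is √(2/220) = 0.095 SD, or 0.095 × √(1 − 0.6²) = 0.076 SD if baseline correlates 0.6 with the outcome. Even 0.046 SD is about half to 0.6 of a standard error, and the differential dropout rates behind it have no support in the documents. This limits the weight of the point but does not remove it.

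Fourth, the extra data are less complete than they look. Counselling use after baseline is listed only at 1 year. The subgroup section says that some students have no examinations that term. Students who intermit may have no grade, and examination-term WEMWBS will usually be missing with CORE-OM. All of this stands and shapes the fix.

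**Conclusion.** The point holds as a weakness in the stated imputation model, not as a demonstrated bias. The named predictors omit records that will be held on non-responders and that plausibly bear on both the missing score and its absence.

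Under the assumptions above, the bias is 0.003-0.007 SD with equal dropout among struggling students and 0.015-0.046 SD with strongly unequal dropout. If controls lose more of them, the estimate moves towards no effect. If the intervention arm loses more, the same mechanism exaggerates the effect. The calculations assume that arm is in the imputation model.

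A reader might infer three stronger conclusions that the documents do not support.

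- That struggling students are imputed as if they were well. Only students who complete the baseline questionnaire are randomised, so all have a baseline CORE-OM, and later scores are used where present. Only distress arising after the last completed score is lost.
- That the primary estimate is materially biased in any case. This needs dropout among struggling students to differ between arms.
- That it is enough for the course to change how many students struggle. With 19% v 14% carrying a record and equal dropout among them, the bias was about 2%.

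**What to change.** In the Statistical methods section, add the following as auxiliary predictors in the imputation model only, and keep them out of the primary analysis model:

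- special circumstances requests and intermission or degrading in the examination term;
- baseline counselling use;
- baseline and postintervention WEMWBS;
- an indicator for having examinations that term, so that the absence of an examination record is read correctly.

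Add counselling use up to the examination term if the service's records are dated, or once the 1-year extract is available. Include record-by-arm terms, or impute separately by arm, where counts allow. Specify this before unblinded results are seen.

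The cost is a few lines in the plan, slightly more analysis work and possibly a dated counselling extract. Participants are not affected. The individual records may be sparse and may need to be combined into one indicator of difficulty. The change does not deal with dropout driven by distress that leaves no trace in any record.
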